### Duration

At least one interim home visit was conducted between enrollment and the start of the intervention when the infant reached 6 months. The first formal assessments (anthropometry and dietary data collection) were obtained at 6 months of age. At this time, the complementary feeding intervention for both groups was initiated and continues through 18 months of age. Follow-up anthropometric assessments are conducted at 9, 12, and 18 months of age. Neurocognitive assessments are performed at 12 and 18 months. Blood samples to assess nutritional status are being obtained from a convenience sample at completion of the trial at 18 months of age.

### Power Analyses

Based on the effect size of 0.5 standard deviation (SD) units observed in another cluster based study of complementary feeding [8], the statistical power for this study was set at 80% to detect a more conservative difference of 0.3 SD in linear growth velocity from 6 to 18 months of age between the intervention and control groups, using a two-tailed test and a 5% Type I error rate.

An ICC = 0.05 was assumed for the sample size calculation. Note that 0.05 is in the upper ranges of ICC values observed in many cluster randomized trials, and would provide the most conservative (i.e., the largest) sample size estimate. Moreover, for a given level of ICC (and Type I and II errors) in a cluster randomized study, increasing the average cluster size reduces the number of required clusters, while increasing the total sample size. This fact, coupled with the consideration that a minimum of 10 clusters are required per treatment group to credibly estimate the ICC with acceptable precision, plus the actual cluster sizes observed in ongoing GN trials, led to an estimated average cluster size of 30.

The above assumptions, an adjustment for 20% attrition over the duration of the study, plus an allowance for cluster loss because of unforeseen reasons such as natural disasters (2 per treatment group), result in a requirement of 20 clusters per treatment group, for a total of approximately 600 subjects per treatment group (40 clusters and 1200 subjects total). Thus, 10 clusters (5 per intervention arm) in each participating country, with approximately 30 subjects per cluster were necessary to achieve desired power.

### Outcome Assessments to Test Hypotheses

Evaluations are undertaken by two teams per site of specially trained community research workers who were recruited from the participating communities. Clusters are randomly assigned to each assessment team, so that each team conducts data collection on both meat and cereal clusters.

The assessment teams are responsible for data collection and measurements for all study participants. The assessment teams do not participate in implementation of the study interventions. Participants' caregivers are asked to come to a central site (e.g. community health center facilities) for assessments.

#### Anthropometry

All measurements are made according to standardized World Health Organization (WHO) guidelines [33]. Anthropometric measurements include naked weight, recumbent length, and head circumference. Naked weights are recorded using a Seca 334 infant scale accurate to 5 grams (Perspective Enterprises, Portage, MI). Recumbent length is measured with a Seca infantometer (model 416, accurate to 1 mm, Perspective Enterprises, Portage, MI). Head circumferences are measured with a plasticized non-elastic measuring tape (accurate to 1 mm) to the nearest 0.1 cm. Each site was provided with the anthropometry equipment. Duplicate measurements are made for each growth parameter. If the two initial measurements differ by more than the pre-determined allowance (0.4 cm, 10 g, and 0.2 cm for length, weight and head circumference, respectively), a third measurement is undertaken. Anthropometric instruments are calibrated regularly.

#### Dietary Data and Infant and Child Feeding Index (ICFI)

Qualitative 24-hour dietary recalls for the previous day [30,31] are obtained at 6, 9, 12 and 18 months. Dietary data collected for the ICFI are: breast feeding (yes/no, number of times per day); bottle/cup feeding (yes/no, number of times per day); numbers of complementary feeds; composition of meals/snacks. This qualitative 24-hr recall is simple to obtain without the assistance of a research nutritionist. From these data, a food variety score and dietary diversity score are calculated. Consumption of micronutrient-fortified products and the administration of supplements are also monitored. The methods used for generating the feeding index scores will be those of Ruel and Menon [31], which have been applied to a large-scale study in Guatemala [34] and have been adapted for use in Sub-Saharan Africa and Pakistan [30].

#### Ages and Stages Questionnaire

The Ages and Stages Questionnaire (ASQ) and ASQ Social-Emotional (ASQ-SE) are verbally administered to all mothers to compare infant neurodevelopment between the two intervention arms at 12 and 18 months. The ASQ, 2^nd ^ed. [35], is a 30-item instrument addressing parent-reported child development in the domains of communication, gross motor, fine motor, problem solving, and personal-social development using age-specific forms. The ASQ-SE scale uses 22-30 items (depending on age) to assess parent-reported child social and emotional functioning in the areas of self-regulation, compliance, communication, adaptive functioning, autonomy, affect, and interaction with people. The ASQ and ASQ-SE assess children in their natural environments to ensure valid results. The questionnaire is available in English, Spanish, and French, and was translated to local dialects for the sites as necessary. A major advantage to the ASQ is its simplicity for administration, which does not require a trained professional, and it has also been used in studies in developing countries [36,37]. Minor modifications have been made to the questions to adapt to local settings. All modifications were reviewed by an external expert in child development who is a consultant to the Global Network.

#### Bayley Scales of Infant Development

The Bayley Scales of Infant Development, 2nd Edition, (BSID II) are administered to assess infant development at 18 (± 0.5) months of age. All sites have obtained a standardized BSID II test kit, instructions and evaluation/scoring forms. The test administration is conducted at each site in a consistent location adapted and arranged to provide a standardized environment for the testing. These are performed by research team members with standardized professional training, to minimize variability within and among clusters. The individuals administering the BSID II at all sites have undergone training by an appropriately trained and experienced professional (e.g. psychologist). Three of the participating sites have prior experience with the BSID II, and past experience within the Global Network has been utilized to conduct standardized training, quality control and assurance of validation and reliability of testing procedures. Video recordings of the administration of the BSID II have been made of each trainee, and these recordings have been reviewed by the child development consultant. For a given site, the same individuals administer the BSID to all participants. To avoid inter-examiner bias, assessment teams have been randomly assigned to complete evaluation visits for meat and cereal clusters. The evaluators administer the BSID directly to each child in the appropriate language using standard material prescribed in the manual, with minimal adaptations made to local settings.

#### Biomarkers of Micronutrient and Inflammation Status

Biomarkers to assess nutritional and inflammatory status include hemoglobin, serum ferritin and transferrin receptor for iron status; serum zinc; serum Vitamin B_12_; and C-reactive protein. Three mL of blood are collected by antecubital venipuncture approximately two hours after eating from a convenience sample of participants (80 from meat and 80 from cereal arms for each country) at 18 months of age (± 2 weeks). Hemoglobin levels are measured immediately utilizing a HemoCue system (HemoCue, Inc., Lake Forest, CA). Blood draws are not obtained from any obviously ill child and, if necessary, are rescheduled within the timeframe above. All laboratory analyses are being performed in Colorado in the Pediatric Nutrition Laboratory (University of Colorado Denver). Standardized procedures have been implemented at each site to assure cold chain integrity between collection and receipt in Colorado.

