## Aim, objectives, and hypotheses

The overall objective of this study is to improve the quality of complementary feeding, and thereby improve growth and development of young children in low resource settings. The specific aim of this project is to determine the impact of a daily intake of meat between 6-18 months of age on linear growth velocity, dietary diversity, brain growth and neurocognitive development, infectious disease morbidity, and micronutrient status in populations traditionally dependent on non-micronutrient fortified plant-based foods for complementary feeding. The comparison group is infants from similar communities who receive an equi-caloric micronutrient fortified rice-soy food supplement.

The *primary hypothesis *is that daily feeding of meat from 6-18 months of age will result in significantly greater linear growth velocity compared to that achieved by daily feeding of an equi-caloric micronutrient fortified cereal supplement with both arms receiving education messages to optimize complementary feeding practices. *Secondary hypotheses *to be tested are that infants consuming meat daily will 1) have higher dietary diversity and variety scores; 2) higher scores on developmental testing; 3) lower rates of infectious disease morbidity; and 4) higher indices of micronutrient status for iron, zinc, and Vitamin B_12_.

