## Methods/design

### Design

The design is a non-masked cluster randomized controlled efficacy trial of a daily intake of lyophilized beef vs. an equi-caloric daily micronutrient fortified rice-soy based cereal from 6-18 months of age (Figure 1). Mothers and care providers of infants in both groups also receive three education messages during home visits by research workers and through illustrative posters for the home and posted at local health centers to reinforce selected features of WHO recommendations for complementary feeding [11]. An additional message to encourage exclusive breastfeeding until six months and to initiate complementary feeding at six months is given at the time of recruitment when the infants were three to four months of age.

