#### Process evaluation

Exit interviews are conducted at each site after the 18 month visit for a randomly selected subset of participating mothers. The interviews evaluate the mothers' perceptions about the intervention, the education messages, and the overall experience of study participation. External events that could potentially impact the study outcomes are monitored and documented in quarterly reports by the field coordinators and senior investigators at each site.

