### Data analyses

All analyses will be conducted using the intent to treat approach. The primary analysis will be adjusted only for clustering (the community effect). This adjustment for clustering also adjusts for community or site differences. A comprehensive analysis of baseline variables of the two treatment groups will be performed to assess the extent, if any, of baseline imbalances between the two groups of clusters/communities assigned to the two treatment groups, both at the individual and at the cluster levels, to determine the need for adjusting analyses. The baseline variables to be examined include: gender and socioeconomic status (SES), prevalence of exclusive breast feeding at 6 months, birth weight, maternal stature, parity, and site. Imbalances occurring at the cluster level can also be adjusted for by incorporating cluster level covariates, which may be cluster aggregated versions of the co-variables mentioned above.

For analysis of the primary outcome, the WHO Multicentre Growth Reference Study [38] will be used as a comparison. Mean Z-scores at 6, 9, 12 and 18 months for length-for-age, weight-for-age and weight-for-length will be determined as well as changes in Z-scores over 12 months. Linear growth velocity from 6-18 months of age was selected as the primary outcome measure because of its potential to be statistically more powerful than a cross-sectional comparison of length at 18 months alone.

The statistical analyses of the primary outcome and other comparison between treatment groups will use hierarchical or multi-level models to adjust for the cluster randomized design of the study. Hierarchical modeling provides a straightforward framework to accommodate adjustments for potential covariates and confounders, both at the subject level (e.g., birth weight, gestational age, gender, etc.) and at the cluster/community level (average SES at the community level, community access to prenatal and antenatal care, community exposure to other nutrition messages, etc.). For both 18-month and longitudinal outcomes, linear mixed models will be used for continuous outcomes such as growth parameters, whereas generalized linear mixed models will be used for discrete outcomes such as frequency of various nutritional intakes and incidence of morbidities.

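### Secondary hypothesis 4 (iron, zinc and B12 status) is tested on a convenience sample in a non-masked trial, so who is bled is not protected by randomisation

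*Protocol article*

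**What the plan says.** All references are to the protocol article.

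- *Biomarkers of Micronutrient and Inflammation Status*: blood is drawn "from a convenience sample of participants (80 from meat and 80 from cereal arms for each country) at 18 months of age". *Duration* repeats the method: "Blood samples to assess nutritional status are being obtained from a convenience sample at completion of the trial at 18 months of age".
- *Aim, objectives, and hypotheses*: these samples serve secondary hypothesis 4, that meat gives "higher indices of micronutrient status for iron, zinc" and vitamin B12. No other source of these indices is described.
- *Design*: "The design is a non-masked cluster randomized controlled efficacy trial".
- *Biomarkers*, on illness: "Blood draws are not obtained from any obviously ill child and, if necessary, are rescheduled within the timeframe above". Secondary hypothesis 3 expects "lower rates of infectious disease morbidity" in the meat arm.
- *Data analyses*: "All analyses will be conducted using the intent to treat approach". Comparisons use multilevel models.
- *Outcome Assessments to Test Hypotheses*: assessment teams are separate from the intervention staff, and each team covers clusters of both arms. They are not described as masked.
- Random selection is used elsewhere. *Cluster Randomization and Sampling* and *Study Subjects and Enrollment* describe a randomly selected recruitment list generated by the data coordinating center (DCC). *Process evaluation* says: "Exit interviews are conducted at each site after the 18 month visit for a randomly selected subset of participating mothers".

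**The concern.** The quota fixes how many children are bled per arm and country. It does not fix which children, or from which clusters. Families know which food they were given, and the trial does not claim masked assessors. If the children who are easy to bleed differ between meat and cereal clusters in a way related to iron, zinc or B12 (through adherence, ease of access or recent illness), the difference between arms mixes the effect of the food with the effect of selection. A multilevel model accounts for correlation within clusters. It does not account for who entered the sample.

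The rule on ill children adds a possible route. Illness is itself a hypothesised outcome of the food, so deferrals and missed draws may differ by arm. The rule is not questioned here; its consequences only need to be counted.

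A smaller point is precision. Without a quota by cluster, the 80 can be drawn unevenly, which raises the design effect.

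**Working it through.** **1. The plan's own sample size.** Inputs from *Power Analyses*: 0.3 SD, two-sided 5%, 80% power, ICC 0.05, cluster size 30, 20% attrition, 2 spare clusters per arm.

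- Individuals per arm: 2 × (1.960 + 0.842)² / 0.3² = 174.4, so 175.
- Design effect: 1 + 29 × 0.05 = 2.45. Then 175 × 2.45 = 428.75, so 429.
- Attrition: 429 / 0.8 = 536.25. Divided by 30 this is 17.9, so 18 clusters. Adding 2 gives 20 clusters, or 600 children per arm.

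This reproduces the stated figure. It concerns linear growth; the article gives no corresponding basis for the 80.

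**2. Share sampled.** Each arm in each country has 5 × 30 = 150 children planned, or 120 after 20% attrition.

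- 80/150 = 53% and 80/120 = 67%, so 47% or 33% are left out.
- Over four countries: 4 × 80 = 320 per arm and 640 in total. 640/1200 = 53% and 640/960 = 67%.

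**3. How uneven the clusters can be.**

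- With 30 per cluster, two clusters supply at most 60, so at least three are needed. The extreme is 30 + 30 + 20.
- With 24 per cluster after attrition, three supply 72, so at least four are needed. The extreme is 24 + 24 + 24 + 8.

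Design effect = 1 + (Σm²/Σm − 1) × ICC. Effective n = 320 / design effect. Detectable difference at 80% power = 2.802 × √(2 / effective n). The ICC of 0.05 was set for growth; using it for biomarkers is an assumption.

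| Draw per arm and country | Clusters per arm | Σm²/Σm | Design effect | Effective n per arm | Detectable difference | Power at 0.3 SD |
|---|---|---|---|---|---|---|
| 16 from each of 5 | 20 | 16 | 1.75 | 183 | 0.29 SD | 82% |
| 24 + 24 + 24 + 8 | 16 | 22.4 | 2.07 | 155 | 0.32 SD | 75% |
| 30 + 30 + 20 | 12 | 27.5 | 2.33 | 138 | 0.34 SD | 70% |

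For an ICC from 0.01 to 0.10, power runs from 94% to 67% (even), 93% to 57% (four clusters) and 92% to 51% (three clusters). These are normal approximations.

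**4. Selection, as an illustration.** Suppose that in one arm only, the tendency to be sampled correlates ρ with the biomarker. Selecting a fraction p then shifts that arm's mean by ρ × φ(z)/p SD, where z is the normal cut-off that leaves p above it. The values of ρ are assumptions.

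| p | φ(z)/p | ρ = 0.1 | ρ = 0.2 | ρ = 0.3 |
|---|---|---|---|---|
| 53% | 0.745 | 0.075 | 0.149 | 0.224 |
| 67% | 0.545 | 0.055 | 0.109 | 0.164 |

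With an even draw, the standard error of the difference is √(2 × 1.75 / 320) = 0.105 SD. With no true effect, a bias of 0.10 SD gives a two-sided rejection rate of about 16%, and 0.15 SD about 30%, against the nominal 5%.

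**The case against.** The case on the other side has real weight.

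- *Whole clusters carry the arm.* Choosing among children within a cluster never means choosing between arms. Quota, age window, timing after feeding and the illness rule are the same in both arms, and assessment teams cover both. Bias needs a selection pattern that differs by arm and relates to the biomarker. This stands, and it is why the point is a risk. These safeguards balance numbers and examiners, but not which children are bled.
- *Selection that works alike in both arms* mainly limits whom the result applies to. This also stands. The limit matters if easily reached families also adhere better, because the foods differ in the nutrients measured (Table 1, 6 to 12 months: iron 5.5 mg in cereal and 1.4 mg in beef). The estimate would then describe better adherers.
- *Intent to treat.* A reader might infer a contradiction with the analysis section. There is none: sampled children can be analysed as allocated. What is missing is protection of the subsample, not of the allocation.
- *Who selects.* A reader might infer that staff who know the arm hand-pick the children. The article does not say who selects or how.
- *Concentration.* A reader might infer that each quota could be filled from one or two clusters. The cluster sizes rule this out, as step 3 shows.
- *Practicality.* A timed venipuncture with cold-chain handling is harder to arrange than an exit interview, and 16 of about 24 completers is a high fraction. If many decline, a random order helps less. This is a reason to record non-draws, not to leave selection open.

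**Conclusion.** The point holds as a should-fix, limited to secondary hypothesis 4. Convenience sampling is the method the article states, in two places, so this is not a detail left to a fuller document. In a non-masked trial it leaves the comparison of iron, zinc and B12 status open to selection, with 33% to 47% of children outside the sample.

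The documents do not show that bias occurred or in which direction. The bias sizes in step 4 rest on assumed correlations acting in one arm only. The loss of precision from uneven clusters is moderate and bounded: 12 to 16 of 20 clusters per arm at worst, and power of 70% to 75% against 82%, if the growth ICC of 0.05 applies. Linear growth velocity, the primary outcome, is measured in all participants and is not touched.

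**What to change.** **Remaining draws.** Replace the convenience sample with a DCC-generated random order within each cluster:

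- Aim for about 16 per cluster (5 × 16 = 80), and approach the next listed child when one is not available.
- If a cluster is lost or its list runs out, spread the shortfall over the remaining clusters of the same arm and country. With one cluster lost this is 4 × 20 = 80.
- Record refusals, deferrals for illness and other non-draws by arm.

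**Children already bled.** Compare sampled with unsampled children by arm on the baseline variables already listed in *Data analyses*, adjust for differences, and state in the report that this comparison rests on a non-random subsample. Adjustment reduces the problem but cannot restore randomisation.

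**Cost.** A list from the DCC, a change of wording, a short non-draw log and some repeat invitations. The number of blood draws stays the same. The article describes sampling as under way, so only part of it may still be open to change.

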#### Infectious Disease Morbidity

Data on incidence and duration of infant diarrhea (more than 3 watery stools per day) are collected weekly from 6 to 18 months based on mother's recall. The mothers are also asked several questions regarding presence of respiratory symptoms (cough, tachypnea/dyspnea, lower chest wall in-drawing and fever) to assess for lower respiratory infection, and regarding symptoms suggestive of malaria. These data are collected in the home by the community coordinators.

#### Process evaluation

Exit interviews are conducted at each site after the 18 month visit for a randomly selected subset of participating mothers. The interviews evaluate the mothers' perceptions about the intervention, the education messages, and the overall experience of study participation. External events that could potentially impact the study outcomes are monitored and documented in quarterly reports by the field coordinators and senior investigators at each site.

### Data management

Data forms are completed using pen and paper. Completed data forms are collected and reviewed weekly by the field supervisor at each research site. Reviewed forms are keyed into a data management system developed by the DCC (RTI). Research sites store data in a stable and secure server, with redundant power supplies, dual network cards, redundant hard drives, and a semi-automated backup procedure to backup server data on a daily basis. Data are transferred from the field sites to the DCC at least once a week using an automated file transfer system. All database files are password protected, compressed, encrypted and signed with a unique digital certificate using public key cryptography before transmission, providing strong protection during transmission.

The DMS includes a variety of data validation, including range checks, data type checks and customized skip patterns. Multiple languages (e.g., English, Spanish, and French) are supported, allowing local data entry personnel to view and enter data in their native language. Data validation is performed both as data are entered and when each form is saved. Validation errors are recorded in a data table for later analysis. A running journal of all data entry is kept, allowing the system to be rolled-back to any given point in time.

The DMS includes reports to assist with project management that can be generated by the research sites. These include reports on complete and incomplete forms, missing forms, scheduled appointments, and errors. Like other parts of the system, all reports are available in the native language.

The DCC converts the databases from Microsoft Access into SAS for analysis. For each database, a SAS program is written which converts the Access database to SAS files, creates date and time variables, and assigns labels and formats to each variable. The SAS files are then stored on the project share in the appropriate protocol directory. These programs are run automatically each time RTI receives a data transmission.

